#### Data monitoring

2.9.4

There is no data monitoring committee designated to this trial. Any adverse and serious adverse events will be immediately reported to the principal investigator and the primary sponsor. An interim analysis will be performed after 20 patients in each study group will have completed 3-month follow-up. All AEs and SAEs will be immediately reported to the local ethics committee, study director, and the sponsors.

### Ethics and dissemination

2.10

#### Research ethics approval

2.10.1

This study follows the Declaration of Helsinki on medical protocols and ethics; all documents of the trial have been approved by the local Ethics Committee of Sechenov University (reference No. 04-19, 03/06/2019).

#### Protocol amendments

2.10.2

Any protocol amendments that may influence the conduct of the study, will be communicated to the local ethics committee and study director, and will be uploaded to clinical trials.

#### Consent or assent

2.10.3

A member of the research team will obtain the consent form. All participants will be able to address their questions about the study to one of the members of the research team.

#### Confidentiality

2.10.4

All patient data will be secured at the study site. No one apart from the members of the research team will have access to any patient data, including anonymized eCRFs with a coded ID, as well as filled out questionnaires.

#### Access to data

2.10.6

No one apart from the members of the research team will have access to the final trial dataset.

#### Dissemination policy

2.10.7

Trial results will be e-mailed to all participants of the trial. Trial results will be disseminated to healthcare professionals via publication in a peer-reviewed scientific journal and by mass media, as well as conference papers to inform the public and stakeholders, and will be uploaded to the primary registry. We have no intention of granting public access to the full protocol, participant-level dataset, and statistical code.

## Discussion

3

This is the 1st prospective randomized clinical trial comparing the efficacy and safety of 2- and 3-row-stapling techniques in LAR for rectal cancer. This study will primarily focus on short-term outcome assessment that will allow to gather preliminary information about the use of 3-row circular staplers in rectal cancer surgery.

The design of this study has certain limitations. Firstly, there is no definitive way to exclude all the preoperative and intraoperative risk factors of AL due to their large number and the presence of nonmodifiable risk factors, such as male gender, the need for preoperative chemo-/radio-/chemoradiotherapy, or tumor size. Moreover, broadening of exclusion criteria with regard to modifiable risk factors, such as tobacco use would hinder patient recruitment significantly, and thus would delay the acquisition of definite conclusions. Additionally, whether open or minimally invasive, TME ends with rectum transection below the inferior tumor margin using a linear cutter stapler followed by colorectal anastomosis formation with a circular stapler. Thus, the quality of both linear mechanical suture on the rectal stump and of the circular stapled anastomosis between the proximal colon and the distal rectal stump influence the integrity and healing rate of colorectal anastomosis. However, in the context of this study the distance of anastomosis from the anal verge is limited to LARs, which will help to achieve homogeneity of the study groups.

Another issue is the uncertainty of the definition of AL. In this protocol, we have referred to the definition of AL proposed by the International Study Group of Rectal Cancer describing it as a “communication between the intra- and extraluminal compartments owing to a defect of the integrity of the intestinal wall at that anastomosis between the colon and rectum or the colon and anus.”^[14]^ Because there are numerous definitions of AL, diagnostic approaches vary greatly between different studies. However, the algorithm of AL diagnosis outlined in this paper allows to detect both clinically significant and asymptomatic forms of AL ensuring adequate primary outcome assessment.

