### Eligibility criteria

2.2

To be eligible for randomization, an individual must comply with all of the following criteria:

Inclusion criteria

1.1.Provision of signed and dated informed consent form1.2.Stated consent to comply with all study procedures and availability for the duration of the study1.3.Male or female1.4.For females of reproductive potential: not pregnant at the time of screening1.5.For males of reproductive potential: use of condoms or other methods to ensure effective contraception with partner1.6.Histologically proven primary rectal adenocarcinoma located within 5 to 15 cm from anal verge not involving internal and/or external sphincter muscle

Exclusion criteria

2.1.Preoperative and intraoperative2.1.1.Current use of antiplatelet drugs, acetylsalicylic acid, or anticoagulants within 7 days prior to intervention2.1.2.Unresectable tumor, inability to perform a TME with colorectal anastomosis, inability to complete R0 resection, or presence of T4b tumor necessitating a multiorgan resection2.1.3.Inability to save the left colic artery2.1.4.Diameter of rectal lumen is unable to contain the working part of the stapler2.1.5.Infection requiring antibiotic treatment within 30 days prior to intervention2.1.6.Anal incontinence prior to surgery (Wexner continence grading scale ≥10)

Postoperative

2.2.1.Inability to complete all the trial procedures2.2.2.Death due to causes unrelated to anastomotic leak in early postoperative period2.2.3.Patient wants to withdraw from the clinical trial

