##### Open approach

2.3.3.1

A midline laparotomy is performed. After an examination of the abdominal cavity and the pelvic cavity, mobilization of the sigmoid colon in the lateral-medial direction begins. Para-aortic lymph node dissection is performed and inferior mesenteric artery is skeletonized with preservation of the integrity of preaortic and prehypogastric plexuses. The inferior mesenteric artery is ligated below the origin of the left colic artery; the latter is preserved. The inferior mesenteric vein is cut at the level of the superior edge of the body of the pancreas. The mesentery of the sigmoid colon is cut in the direction of the intestinal wall. The place of the transection of the sigmoid colon is determined at a distance of at least 15 cm above the tumor in an area with an adequate blood supply. Sigmoid colon is divided and the circular stapler anvil is fixed in its stump with a purse-string suture. After that, a TME is performed with the preservation of the hypogastric nerves and pelvic nerve plexuses. L-shaped clamp is applied to the rectum at least 2 cm below the tumor. From the side of the perineum, the rectal stump is washed with an antiseptic solution. After that, below the L-shaped clamp, a linear cutter stapler is applied and the rectum is transected. The surgeon inserts the circular suturing device into the anal canal. Under the guidance of a direct observation, the trunk of the operating part of the device is pierced in the area of one of the edges of the suture line of the rectal stump. The stump of the sigmoid colon is moved to the pelvic cavity, the rod of the device anvil is put on the trunk of the operating part, and end-to-end colorectal anastomosis is formed. The height of the anastomosis is measured (in centimeter from the edge of the anal canal). After the removal of the circular suturing device, the integrity of the resected intestinal rings is checked. The suture line is tested for leakage. A transanal silicone tube is installed. A preventive transverse colostomy is formed. A silicone drain tube is installed in the pelvic cavity. The laparotomy wound is sutured. Sterile dressings are applied.

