##### Laparoscopic approach

2.3.3.2

Following trocar installation and examination of abdominal cavity and pelvic cavities, para-aortic lymph node dissection is performed with the skeletonization of the inferior mesenteric artery and preservation of the integrity of the preaortic and prehypogastric plexuses. The inferior mesenteric artery is divided below the origin of the left colic artery; the latter is preserved. The sigmoid colon and the distal portion of the descending colon are mobilized in the medial-lateral direction. The inferior mesenteric vein is cut at the level of the upper edge of the body of the pancreas. After that, a TME is performed with the preservation of the hypogastric nerves and pelvic nerve plexuses. The rectum is transected with a linear cutter stapler at least 2 cm below the inferior margin of the tumor. A mini-laparotomy is performed. In the wound, the separated rectum and the sigmoid colon are removed, the mesentery of the sigmoid colon is transected in the direction of the transection of the intestinal wall. Sigmoid colon is divided and the circular stapler anvil is fixed in its stump with a purse-string suture. The stump of the intestine with circular suturing device anvil is immersed in the abdominal cavity, the laparotomy wound is sutured. A repeated laparoscopy is performed. From the side of the perineum, after preliminary washing of the rectal stump, the surgeon inserts the circular suturing device into the anal canal. Under guidance with a laparoscope, the trunk of the working part of the apparatus is pierced in the area on one of the edges of the suture line of the rectal stump. The sigmoid colon stump is moved to the pelvic cavity, the rod of the device head is inserted into the trunk of the operating part, an end-to-end colorectal anastomosis is secured. The height of the anastomosis is measured in centimeter from the anal verge. After the removal of the circular suturing device, the integrity of the resected intestinal rings is assured. The suture line is tested for leakage. A transanal silicone tube is installed. A preventive transverse colostomy is formed. A silicone drain tube is installed in the pelvic cavity. Abdominal wall openings are sutured. Sterile dressings are applied.

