#### Allocation

2.8.1

Participants will be randomly assigned to either control or experimental group with a 1:1 allocation ratio using fixed block randomization with a computerized random number generator. The block size equals at least 4 and will be unknown to the principal investigator, outcomes assessor and the operating surgeon. Because the possibility of making a stapled anastomosis will only be determined intraoperatively by the operating surgeon with respect to exclusion criteria precluding stapled anastomosis formation, all subjects will be allocated intraoperatively.

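### Restriction to LAR is said to help make the groups alike in anastomotic distance, but no criterion limits that distance and no stratum is named: a cheap improvement missed, not a bias

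*Protocol article*

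**What the plan says.** - **Discussion (section 3).** After conceding that many leak risk factors cannot be excluded, the article says that "the distance of anastomosis from the anal verge is limited to LARs, which will help to achieve homogeneity of the study groups".
- **Eligibility (section 2.2).** Criterion 1.6 is "Histologically proven primary rectal adenocarcinoma located within 5 to 15 cm from anal verge not involving internal and/or external sphincter muscle". The exclusions include "inability to perform a TME with colorectal anastomosis, inability to complete R0 resection". Neither gives a limit in centimetres for the anastomosis.
- **Surgery (sections 2.3.3.1 and 2.3.3.2).** In the open operation, "L-shaped clamp is applied to the rectum at least 2 cm below the tumor". In the laparoscopic operation, "The rectum is transected with a linear cutter stapler at least 2 cm below the inferior margin of the tumor". Both are minimum distances. Height is recorded only once the anastomosis exists: "The height of the anastomosis is measured in centimeter from the anal verge".
- **Allocation (section 2.8.1).** The method is 1:1 "fixed block randomization with a computerized random number generator", carried out during the operation. No stratification factor is named.
- **Analysis (Abstract and section 2.9.3).** Leakage is compared by Pearson chi-squared or Fisher exact test. Baseline characteristics are compared to see whether randomisation worked. No adjustment is described.

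**The concern.** The Discussion sentence offers reassurance: some risk factors cannot be controlled, but the restriction to LAR helps keep the arms comparable in anastomotic distance. A reader looking for the rule behind it finds a tumour range of 10 cm, a minimum transection distance and a TME requirement, but no bound on the anastomosis itself. Eligibility also acts on both arms alike. It can narrow the spread of heights in the trial, but it cannot balance the arms over the spread that remains. Stratified allocation or an adjusted analysis would do that, and the article describes neither.

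At stake is how convincing the result will be. The trial is small (77 per arm) and the margin is 5 points. If one arm happens to hold visibly more low tumours, the leakage comparison will be disputed, and the planned baseline tests would show the imbalance without correcting for it.

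**Working it through.** **Inputs from the documents.** 77 per arm, margin 5 points, one-sided alpha 0.05, power 80%, leak rates of 18% and 30% (section 2.6); interim look at 20 per arm (section 2.9.4).

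**Assumptions.** The documents give neither the share q of low tumours nor leak rates by height. I take q = 50% for the main figures (20% and 30% as alternatives) and a leak-risk gap of 10 points (23% low, 13% high) or 20 points (28% low, 8% high), both averaging 18%.

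**1. The plan's own figure.** With unpooled variance, n per arm = (1.645 + 0.842)² × (0.18×0.82 + 0.30×0.70) / (0.12 + 0.05)² = 6.183 × 0.3576 / 0.0289 = 76.5, rounded up to 77, or 154 in total. This requires 30% in the control arm and 18% in the experimental arm, the reverse of how section 2.6 assigns them. That is a separate matter; only n = 77 is used below.

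**2. Chance imbalance in the share of low tumours.** SD = sqrt(2q(1−q)/n).

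| n per arm | q | SD (points) | P(imbalance ≥10 points) | P(imbalance ≥15 points) |
|---|---|---|---|---|
| 77 | 20% | 6.4 | 13% | 2% |
| 77 | 30% | 7.4 | 19% | 4% |
| 77 | 50% | 8.1 | 23% | 6% |

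At 20 per arm, an imbalance of 10 points or more has a probability of 55% to 64% over the same range of q.

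**3. Effect on the leak difference (q = 50%, n = 77).** The 95% range of the imbalance is ±1.96 × 8.06 = ±15.8 points.
- Gap of 10 points: 15.8 × 0.10 = ±1.6 points (one SD: 0.8).
- Gap of 20 points: 15.8 × 0.20 = ±3.2 points (one SD: 1.6).

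**4. Gain from stratifying and analysing by stratum.** The overall variance per patient is 0.18×0.82 = 0.1476.
- Gap of 10: 0.5×(0.13×0.87) + 0.5×(0.23×0.77) = 0.1451, which is 1.7% lower.
- Gap of 20: 0.5×(0.08×0.92) + 0.5×(0.28×0.72) = 0.1376, which is 6.8% lower.

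**5. Is the shift extra to the sampling error?** With 18% in both arms, the variance of the leak difference is 2×0.1476/77 = 0.003834, so the SE is 6.2 points (6.8 with 18% and 30%). The variance of the shift in step 3 is (0.0806×0.10)² = 0.000065 or (0.0806×0.20)² = 0.000260. Dividing by 0.003834 gives 1.7% and 6.8%, the same shares as in step 4. The shift is thus a component of the ordinary sampling variance, and the unadjusted confidence interval already covers it.

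**The case against.** The strongest reply is that nothing here is an error. The sentence says only that the restriction will help, in a paragraph about limitations. Requiring a feasible TME with colorectal anastomosis, and no sphincter involvement, does narrow the population. Every unstratified covariate is left to chance in a valid randomised trial. The gain of 2% to 7% in variance is only about 1% to 3.5% in the SE. All of this stands.

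Four further points also carry weight:
- Subtracting 2 cm from the tumour range suggests anastomoses from about 3 to 13 cm. A reader might take that as what the protocol admits, but TME tends to bring anastomoses lower, and the documents do not show that the upper end occurs.
- The stratifier available before allocation is tumour height. It is only a proxy for anastomotic height, and a weaker one where TME lowers the anastomosis regardless of the tumour's position.
- The Discussion names other risk factors (sex, preoperative therapy, tumour size, tobacco) and gives no effect size for height.
- The article is a condensed account. Silence on strata does not rule them out, and covariate adjustment is commonly left to the analysis plan.

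The reply does not remove the mismatch between the Discussion sentence and the criteria. The article itself chose anastomotic distance as the factor on which it wants comparable groups, and the allocation it describes does nothing to secure that.

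**Conclusion.** The point holds as a modest design improvement and a wording correction. Restriction to LAR with TME may narrow anastomotic distance, but no criterion limits it, and balance between the arms depends on randomisation alone.

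Two stronger readings are tempting, and the documents support neither. One is that the protocol claims its criteria make height homogeneous; it says only that the restriction will help. The other is that missing stratification biases the comparison or invalidates the design. Unstratified block randomisation is unbiased in expectation, and step 5 shows that the chance shift is already inside the sampling error. Setting it against the 5-point margin as an additional threat would count it twice.

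The benefit available is about 2% to 7% of the variance, with protection against chance shifts of about 1.6 to 3.2 points (95% range). These sizes rest on an assumed 50:50 split and assumed leak-risk gaps of 10 to 20 points by tumour height.

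**What to change.** 1. Stratify the intraoperative block randomisation by tumour height from the anal verge at screening, in two bands, for example 5–10 cm and >10–15 cm. The value must be known to apply criterion 1.6, and screening includes sigmoidoscopy and pelvic MRI (section 2.3.1), so it is available before allocation.
2. Carry the stratum into the primary risk-difference estimate. If the allocation list can no longer be changed, at least adjust the primary risk difference for tumour height, specified before unblinding.
3. Reword the Discussion sentence to state the tumour range that criterion 1.6 admits, and to say that anastomotic height is recorded but not limited.

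**Cost.** One factor in the computer-generated list and one sentence of text, with no extra patients or procedures. The downside is two block lists to run and a slightly higher chance of incomplete blocks at the end of recruitment.
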